## Abstract

**Introduction:**

Repetitive transcranial magnetic stimulation (rTMS) is an evidence-based treatment widely recommended to promote hand motor recovery after ischaemic stroke. However, the therapeutic efficacy of rTMS over the motor cortex in stroke patients is currently restricted and heterogeneous. This study aimed to determine whether excitatory rTMS over the contralesional dorsal premotor cortex (cPMd) facilitates the functional recovery of the upper limbs during the postacute stage of severe ischaemic stroke.

**Methods and analysis:**

This study will be conducted as a single-blind, controlled, randomised study, in which 44 patients with poststroke hemiplegia with a course of disease ranging from 1 week to 3 months and Fugl-Meyer upper limb score ≤22 will be enrolled. The study participants will be randomly assigned to groups A (n=22) and B (n=22). The two groups are based on routine rehabilitation training and drug treatment; group A will be treated with low-frequency (1 Hz) rTMS over the contralesional primary motor cortex (cM1), and group B will be treated with high-frequency (10 Hz) rTMS over cPMd. For 2 weeks, rTMS will be administered once a day, 5 days a week. The primary outcome is the Fugl-Meyer assessment of the upper limb. The secondary outcomes include the Arm Subscore of the Motricity Index, Hong Kong edition of Functional Test for the Hemiplegic Upper Extremity, Modified Barthel Index and Modified Ashworth Scale score of the paralysed pectoralis major and biceps brachii. Furthermore, data of diffusion tensor imaging and functional MRI will be collected. These outcomes will be assessed before and after the completion of the intervention.

**Ethics and dissemination:**

This study has been approved by the Ethics Committee of the First Affiliated Hospital of Nanjing Medical University (2020 SR-266). The findings of this study will be spread through networks of scientists, professionals and the general public as well as peer-reviewed scientific papers and presentations at pertinent conferences.

**Trial registration number:**

ChiCTR2000038049

STRENGTHS AND LIMITATIONS OF THIS STUDYThis will be a single-blind, controlled, randomised clinical study to compare high-frequency repetitive transcranial magnetic stimulation (rTMS) over contralesional dorsal premotor cortex (cPMd) and low-frequency rTMS over contralesional primary motor cortex (cM1) in severe ischaemic stroke.We will use neuronavigation to position the site of cPMd and cM1 stimulation.Additionally, various outcome measures, including clinical function and functional MRI, will be included to investigate the therapeutic effects of rTMS and its underlying neuroplasticity mechanisms.Because of low-frequency rTMS to the cM1 ranked as an A-level recommendation for improving motor function after stroke, no blank control group undergoing sham transcranial magnetic stimulation (TMS) will be set up.Given the nature of TMS interventions, blinding operators is not feasible.

## Introduction

Ischaemic stroke has emerged as a critical public health problem as the main contributor to significant long-term impairment.^1 2^ Among them, the age group of 40–70 years is the primary high-risk age range for stroke, which has relative homogeneity, stability and representativeness.^3^ Movement disorders after ischaemic stroke not only reduce the activities of daily living (ADL) and affect the health of patients but also place a heavy strain on the society as a whole.^2 4^ Hypofunction of the upper limbs is one of the most common types of dyskinesia following ischaemic stroke, which seriously affects the patient’s ADL and hampers rehabilitation progression.^5 6^ In ischaemic stroke rehabilitation, improving the upper extremity functional capacity remains a challenging issue.

The effectiveness of repetitive transcranial magnetic stimulation (rTMS) as ischaemic stroke rehabilitation therapy has been thoroughly studied.^6 7^ This technique promotes brain plasticity by providing continuous magnetic pulses to the brain.^8^ After stroke, neuroplasticity-induced cortical reconfiguration is necessary for the restoration of motor performance.^9^ According to widespread consensus, low-frequency (≤1 Hz) rTMS (LF-rTMS) can reduce neuronal activity and cortical excitability, whereas high-frequency (≥5 Hz) rTMS (HF-rTMS) has the opposite effect.^10^ The interhemispheric inhibition (IHI) model is the foundation of the current rTMS intervention method to support the improvement of upper extremity performance in stroke patients.^11^ It indicates that decreased excitability of the lesioned primary motor cortex (M1) region after stroke results from ‘double obstacles’, including the ipsilateral areas and excessive inhibition in the contralateral areas.^12^ Therefore, lowering IHI by minimising the excitation of the contralesional side will improve recovery.^13^ The IHI model currently serves as the foundation for recommendations regarding the application of rTMS in stroke recovery, with low-frequency rTMS to the contralesional M1 (cM1) ranked as an A-level recommendation for improving motor function.^10^ Because the heterogeneity of patients is not taken into account, the clinical efficacy of this rTMS intervention strategy for poststroke motor dysfunction is limited.^10^ However, for patients with severe stroke with low structural retention, using the vicariation model may be preferred, which posits that the activity in the remaining network locations compensates for the loss of certain capabilities in damaged areas.^14^

In patients with severe ischaemic stroke, the dorsal premotor cortex (PMd) of the contralesional hemisphere plays an impressive compensatory role in motor function recovery.^15 16^ PMd has extensive connections to M1 as well as specific motor regions in the cerebral motor connections of the parietal and frontal lobes.^17^ Sankarasubramanian *et al* found that the novel approach of cPMd facilitation (5 Hz rTMS) resulted in more improvement than that of cM1 inhibition (1 Hz rTMS) in severely impaired stroke patients by alleviating interhemispheric competition inflicted on weak iM1.^16^ cPMd reduces inhibition of weak iM1 and provides ipsilateral access (uncrossed corticospinal and brainstem-mediated reticulospinal) to the paralysed limb to aid recovery.^15 18^ Lotze *et al* proposed an inverse correlation between PMd activation and ipsilateral corticospinal tract (CST) integrity, verifying the potential importance of contralateral PMd for good motor performance.^19^ In a study on interhemispheric cPMd-iM1 interactions, Bestmann *et al* used paired-coil transcranial magnetic stimulation (TMS) through concurrent TMS-functional MRI (fMRI) and confirmed that conditioning cPMd pulses had a facilitative effect on ipsilesional M1.^20^ This depends on the rising excitability in ipsilesional sensorimotor areas (BA4p), which maintains direct projections to spinal motoneurons and then increases the motor outputs of the paralysed upper limb.^20^ Therefore, we expect that cPMd, as a potential therapeutic target, can facilitate the rehabilitation of upper extremity movements following ischaemic stroke.

To this end, this randomised controlled clinical trial aims to investigate whether the excitatory rTMS protocol over cPMd has a better effect than the inhibitory rTMS protocol over cM1 to compensate for the limitations of its inconsistent therapeutic effects. In addition to common clinical scales for evaluating upper limb motor function, diffusion tensor imaging (DTI) and fMRI will be used to explore changes in structural and functional connectivity, analyse the correlation between clinical function assessments and neuroimaging data and further elucidate the neurological mechanisms underlying poststroke upper limb rehabilitation.^21^ Several previous investigations have shown that cM1 inhibition does not significantly increase the rehabilitation of upper extremity movements in severe stroke patients.^16 22^ As a result, we hypothesise that the excitatory rTMS protocol over cPMd might be an effective therapy for the recovery of upper extremity motor performance following severe ischaemic stroke. This research may offer significant novel clues into the clinical effects of rTMS in the treatment of upper extremity impairment in ischaemic stroke patients and the underlying neuroplasticity mechanisms of TMS intervention.

## Materials and analysis

This study is a single-blind, controlled, randomised clinical trial with two groups (A and B). The study will be carried out in the Rehabilitation Medicine Centre, the First Affiliated Hospital of Nanjing Medical University, Nanjing, China. Before the trial, detailed information about the research project was provided to potential participants. After the patients voluntarily sign the informed consent form, they will be invited to participate in the trial. The improvement of adherence lies in the need for adequate communication before enrolment, so that the participants completely understand the significance and responsibilities of this study and volunteer to participate.

All eligible participants will be randomly assigned (1:1) to either group A (n=22) or group B (n=22). In consideration of research purposes, ethical perspectives, feasibility and practicality, this study was not designed with a placebo control group. Figure 1 depicts the experiment flowchart. The study protocol has been approved by the Ethics Committee of the First Affiliated Hospital of Nanjing Medical University (2020 SR-266) and registered on Chinese Clinical Trial Registry (ChiCTR2000038049, website: http:// www.chictr.org.cn).

**Figure 1 F1:**
[figure not shown]
Experiment flowchart. FMA-UE, Fugl-Meyer assessment of upper extremity; AMI, Arm Subscore of the Motricity Index; FTHUE-HK, Hong Kong edition of Functional Test for the Hemiplegic Upper Extremity; MBI, Modified Barthel Index; MAS, Modified Ashworth Scale; FA, fractional anisotropy; FAAI, FA Asymmetry Index; rTMS, repetitive transcranial magnetic stimulation; cM1, contralesional primary motor cortex; cPMd, contralesional dorsal premotor cortex.

### Participants

#### Inclusion criteria

The following are the inclusion criteria: (1) ischaemic stroke confirmed by CT and/or MRI meets the diagnostic criteria for cerebral infarction in the cerebrovascular disease; (2) primary or unilateral onset or previous onset without residual neurological dysfunction; (3) stable vital signs and clear consciousness; (4) the age ranges from 40 to 70 years; (5) the course of disease ranges from 1 week to 3 months; (6) paralysis of the upper limbs; (7) FMA-UE score ≤22; and (8) the selected candidate or their relatives sign the informed consent form.

#### Exclusion criteria

The following are the exclusion criteria: (1) epilepsy in the previous, a family history of epilepsy and taking medications that cause seizures; (2) the function of the urinary, cardiovascular, respiratory and other important systems decreases or fails; (3) severe deficits in cognition and communication that impede patient participation during evaluation and therapy; (4) posterior circulation infarction; (5) TMS and fMRI-related restrictions, including a pacemaker, an artificial metal heart valve implant, a drug treatment pump, an insulin pump, an aneurysm clip (other than titanium alloy, which is not paramagnetic) and a metal implant in the body; (6) severe cervical spondylosis includes severe cervical stenosis and cervical spinal instability; (7) complete occlusion of the internal carotid artery; (8) direct injuries and skull defects in the stimulation area; (9) women during pregnancy; (10) severe high fever; (11) claustrophobia; and (12) inability to cooperate with fMRI examination.

### Sample size

The sample size was estimated using GPower (V.3.1.9.7). To evaluate the impact of LF-rTMS protocol over cM1 vs HF-rTMS protocol over cPMd on functional motor performance of the upper extremities evaluated utilising FMA-UE (the primary outcome) over 2 weeks, a sample size of 42 patients (21 per group) completing the intervention will be expected to reach the statistical power of 80% at the significance level of 0.05 (two-sided test), assuming a small-to-moderate effect size of Cohen’s d=0.45.^23^ We will randomise 44 patients (22 in each group) to account for a 5% dropout rate.

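### The protocol claims 80% power at d=0.45 with 21 patients per group; those inputs give about 30%, and 42 patients is the size for an effect twice as large

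*Protocol article*

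**What the plan says.** The Sample size section reports a GPower calculation for the primary outcome, FMA-UE over 2 weeks, comparing the two stimulation protocols: "To evaluate the impact of LF-rTMS protocol over cM1 vs HF-rTMS protocol over cPMd on functional motor performance". Its elements are:

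- Completers and result: "a sample size of 42 patients (21 per group) completing the intervention will be expected to reach the statistical power of 80" per cent.
- Test level: "at the significance level of 0.05 (two-sided test".
- Effect: "assuming a small-to-moderate effect size of Cohen’s d=0.45".
- Randomised number: "We will randomise 44 patients (22 in each group) to account for a 5% dropout rate".

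The section names neither the test family used in GPower nor any pre-post correlation. The Statistical analysis section (Clinical data analysis) plans repeated-measures ANOVA for the primary outcome and rules out multivariable adjustment. The Abstract says outcomes are measured before and after the intervention, so there are two time points.

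**The concern.** The section prints effect, size, test level and power together, so the claim can be checked directly. By the usual rule of thumb, 80% power at d near 0.45 takes close to 80 patients per arm, not 21. A shortfall of that size suggests that the effect entered in the software was not the effect described in the text.

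FMA-UE is the only primary outcome, and the Introduction makes superiority of cPMd stimulation over cM1 stimulation the central question. The comparator is an active, recommended treatment and there is no sham arm. A non-significant result from a trial advertised as having 80% power for a modest effect invites the reading that the two targets perform alike. If the real power is about 30%, such a result would say little.

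**Working it through.** **Inputs, all from the Sample size section:** n=21 completers per arm (22 randomised), two-sided alpha 0.05, d=0.45, claimed power 80%.

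**1. Attempt to reproduce the stated figure (two-sample t-test).** Degrees of freedom are 2n−2 = 40 and the noncentrality is δ = d·√(n/2) = 0.45·√10.5 = 1.458. Power is the probability that a noncentral t with 40 df and this δ exceeds the two-sided critical value.

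| Case | Power |
|---|---|
| 21 per arm, exact t | 29.6% |
| 21 per arm, normal approximation Φ(1.458−1.960) | 30.8% |
| 22 per arm, exact t | 30.8% |
| 21 per arm, one-sided 0.05 (not what is planned) | 41.6% |

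The stated 80% is not reproduced.

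**2. Size needed at d=0.45.** Normal approximation: n = 2(1.960+0.842)²/0.45² = 77.5, so 78 per arm. Exact t: 78 per arm gives 79.7% and 79 per arm gives 80.3%. So 79 per arm, 158 completers, are needed.

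**3. Effect that 21 per arm can detect.** Solving the exact t power for 80% gives d=0.886. At d=0.90, δ = 0.90·√10.5 = 2.916 and power is 81.2%.

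**4. Routes that do return N=42.**

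- *0.45 entered as Cohen's f in a two-group ANOVA.* λ = f²N = 0.2025·42 = 8.505. N=40 gives 79.2% and N=42 gives 81.2%. With two equal groups d=2f, so this is d=0.90.
- *Repeated-measures within-between interaction, f=0.225, m=2 measurements, ρ=0.5.* λ = f²·N·m/(1−ρ) = 0.050625·42·2/0.5 = 8.505, the same λ and the same 79.2% and 81.2%. In a 2×2 interaction the between-group difference in change is 4f = 0.90 SD. A difference in change of 0.45 SD is f=0.1125, with λ = 2.126 and power 29.6%.
- *Paired t-test on 42 patients at d=0.45.* Power is 81.3% (41 patients give 80.3%). This tests change within one group, not the difference between groups.

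**5. Can the pre-post correlation rescue the figure?** With two time points, the group-by-time test is a t-test on change scores. If d=0.45 is scaled on the cross-sectional SD, the effect on the change scale is 0.45/√(2(1−ρ)). For ANCOVA it is 0.45/√(1−ρ²). The protocol gives no ρ, so a range is shown for 21 per arm:

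| Assumed ρ | Change score / group-by-time | ANCOVA |
|---|---|---|
| 0.3 | 22.5% | 32.0% |
| 0.5 | 29.6% | 37.6% |
| 0.7 | 45.1% | 51.3% |
| 0.8 | 61.4% | 66.0% |
| 0.9 | 88.9% | 90.4% |

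For 80% power the change-score analysis needs ρ = 1−(0.45/0.886)²/2 = 0.87, and ANCOVA needs ρ = √(1−(0.45/0.886)²) = 0.86. If the group main effect were tested instead (f=0.225), power would be at most 52.1% (ρ=0) and would fall as ρ rises.

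**6. Dropout.** 42/0.95 = 44.2, so randomising 44 is close enough and is not at issue.

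**The case against.** The strongest reply is that the section does not name the test, while the planned analysis is a repeated-measures ANOVA with a baseline and a post-treatment value. Power for that analysis depends on how d was standardised and on the pre-post correlation, and a condensed article may leave both to the full protocol. On this view 30% is not established for the planned analysis either, and where 42 came from is a guess, since several routes fit.

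Part of this stands. The 30% figure belongs to a two-group comparison at d=0.45, or to change scores at ρ=0.5; a higher correlation with d on the raw-score SD would raise it. The origin of 42 is an inference. The article also nowhere says that a null result will be read as equivalence, so that is a risk and not a plan.

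It does not save the claim. The section states its inputs and output as complete, and they disagree. The two between-group routes that return 42 both power a 0.90 SD difference, and the paired route answers a different question. The rescue by correlation needs an unstated value close to 0.87; at the value of 0.5, which does reproduce 42 with f=0.225, the effect powered is still twice the one described.

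**Conclusion.** The power statement is wrong as written. At the stated effect, 21 completers per arm give 29.6% power, so the chance of missing a true difference of 0.45 SD is 70.4% against the 20% implied. The design has 80% power for about 0.89 SD, which is a large effect and not a small-to-moderate one.

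These figures assume a two-sided 5% test, equal arms, and d as the between-group difference in SD units of the variable tested. If d refers to the raw-score SD and group-by-time is tested, power is 30%, 45% and 61% at correlations of 0.5, 0.7 and 0.8, and reaches 80% only at about 0.87. Which error produced 42 cannot be settled from the article, and the conclusion does not depend on it.

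**What to change.** Retrieve the GPower run, then correct the Sample size section without changing enrolment. Suggested text: *With 42 completers (21 per group) and a two-sided 5% test, the trial has 80% power to detect a between-group difference in FMA-UE change of about 0.89 SD; power for a difference of 0.45 SD is about 30%.* Drop the small-to-moderate label.

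If the run used Cohen's f or an assumed pre-post correlation, state the test, the effect-size definition, the correlation and its source, and give the power that follows for a difference expressed in one clearly named SD.

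It would also help to commit to reporting the estimated difference with its 95% confidence interval and to not reading a non-significant result as evidence of equivalence.

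The cost is a few sentences and a less favourable power statement. No additional patients and no design change are needed.

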### Randomisation and blinding

After the baseline assessment is completed and the inclusion/exclusion criteria are checked, the participants will be randomised into group A or B (ratio 1:1) using SPSS software to generate random sequences. The stratification criterion is the course duration of the disease, with two strata: 1 month and 2–3 months. This study is a single-blind study. However, the evaluators who perform the measurements will be blinded to the group to which the participants belong. Special personnel are responsible for randomisation, assessment and intervention, respectively.

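### The two randomisation strata for disease duration have no stated boundary, so the stratum of a patient between 1 and 2 months is ambiguous

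*Protocol article*

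**What the plan says.** - **Eligibility.** Item 5 of the Inclusion criteria reads "the course of disease ranges from 1 week to 3 months". The Methods and analysis paragraph of the abstract gives the same window: patients "with a course of disease ranging from 1 week to 3 months and Fugl-Meyer upper limb score ≤22 will be enrolled".
- **Allocation.** Under Randomisation and blinding, once baseline assessment and the eligibility check are done, "the participants will be randomised into group A or B (ratio 1:1) using SPSS software to generate random sequences".
- **Strata.** The same section continues: "The stratification criterion is the course duration of the disease, with two strata: 1 month and 2–3 months". No other stratification factor is named.
- **Size.** The Sample size section states: "We will randomise 44 patients (22 in each group) to account for a 5% dropout rate".
- **Analysis.** The Clinical data analysis section plans repeated-measures analysis of variance. It rejects multivariable adjustment because the trial is randomised, so the primary model has no covariates.

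**The concern.** Strata should partition the eligible population: every eligible patient belongs to exactly one. Here the eligibility window and the strata use the same variable, but the stratum labels jump from 1 to 2 months while the window has no break. A patient at 6 weeks is plainly eligible, yet the text does not settle where that patient goes.

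Disease duration is the only stated device for prognostic balance beyond randomisation itself. With 22 patients per group, placing similar patients in different strata weakens the balance that stratification is meant to give. A primary analysis without covariates would not correct any imbalance on duration that resulted.

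This is not detail that a condensed article may leave to a fuller document. The article states the strata, and as stated they do not clearly fit the stated window. The boundaries are also needed before the first allocation, so a later analysis plan cannot supply them.

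**Working it through.** The plan gives no figure on this point to reproduce. The check compares the stratum intervals with the eligible interval.

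**Inputs**
- Eligible window: 1 week to 3 months (Inclusion criteria, item 5; abstract).
- Strata: 1 month; 2–3 months (Randomisation and blinding).
- Number randomised: 44 (Sample size).
- Assumption: one month = 365.25/12 = 30.44 days.
- Assumption, for patient counts only: enrolment is uniform over the window.

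**Step 1. Length of the window.** 3 × 30.44 = 91.31 days; 91.31 − 7 = 84.31 days.

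**Step 2. Elapsed-time reading** (up to 1 month; from 2 to 3 elapsed months).
- First stratum: 30.44 − 7 = 23.44 days. Second stratum: 30.44 days.
- Covered: 23.44 + 30.44 = 53.88 days; 53.88/84.31 = 63.9%.
- Not covered, between 1 and 2 months: 30.44/84.31 = 36.1%.
- With 30-day months the result is the same: 30/(90 − 7) = 36.1%.

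**Step 3. Patients in that gap.** 0.361 × 44 = 15.9, about 16. Without uniform enrolment the count moves: if 20% of patients fell there, 0.20 × 44 = 8.8, about 9; if 50%, 0.50 × 44 = 22.

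**Step 4. Month-count reading** (first month; second and third months).
- First stratum: 23.44 days. Second stratum: 91.31 − 30.44 = 60.87 days.
- Covered: 23.44 + 60.87 = 84.31 days, the whole window. Patients without a stratum: 0.

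**Step 5. One ordinary patient, 6 weeks after onset.** 42/30.44 = 1.38 months.

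| Reading of the labels | Stratum of the 6-week patient | Part of the window left out |
|---|---|---|
| Elapsed-time ranges | neither | 1 to 2 months, 36.1% |
| Month of the course | 2–3 months (second month) | none |
| Completed months | 1 month (one completed) | under 1 month, 23.44/84.31 = 27.8% |

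Three ordinary readings give three answers for the same patient, and the document does not choose between them. The sample size is not affected under any of them.

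**The case against.** The strongest reply is that the labels count months of the disease course. The first month, then the second and third, tile a window that ends at 3 months, and two labels 1 and 2–3 fit that better than a scheme that omits the middle third. The 36% figure also needs a mixed reading: 1 month as a range that reaches back to 1 week, but 2–3 months as exact elapsed time. This stands in part. The authors may well have meant a month count, and then nobody is unclassified. But the text does not say so, and the eligibility criterion states its own limits, 1 week and 3 months, as elapsed time for the same variable. The reply reduces the point from a proven gap to an ambiguity; it does not remove it.

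A reader might also infer several stronger things that the documents do not support:

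- **That the person randomising can steer allocation by choosing the stratum.** This would need a case-by-case choice and a foreseeable next assignment. The article describes neither, and it says that separate personnel handle randomisation, assessment and intervention, with blinded evaluators. Within whichever stratum is used, treatment would still be assigned at random.
- **That the stratum could not be used in an analysis.** Eligibility requires disease duration to be known, so it can be recut later.
- **That duration was chosen because early patients recover more.** The article gives no reason for the choice.

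**Conclusion.** The stratification rule is ambiguous as written and should be corrected. Between 0 and about 16 of 44 patients could be unclassified: 0 if the labels count months of the course, about 16 if they are elapsed time and enrolment is uniform over 1 week to 3 months. Under the elapsed-time reading, other enrolment patterns would change the upper figure (9 to 22 if 20% to 50% of patients fall between 1 and 2 months).

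It would overstate the point to say that these patients certainly have no stratum, since one natural reading closes the gap. The likely consequence is weaker balance on the only stated stratification factor, left uncorrected by the unadjusted primary analysis. Selection bias is not shown.

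**What to change.** **Randomisation and blinding.** Replace the two labels with contiguous, non-overlapping strata in days from stroke onset that cover the whole eligible window, for example 7–30 days and 31 days to 3 months, with 3 months defined exactly as in the inclusion criterion. State that each patient's stratum is set from the recorded onset date before the allocation is drawn. If recruitment has begun, document the rule actually applied, including how patients between 1 and 2 months were placed. This is a one-line change with no burden on patients and no effect on the sample size.

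**Clinical data analysis (a separate change).** Include the stratification factor in the primary model and amend the statement that rules out covariates. If the treatment effect is read from the group-by-time term, the factor should enter with its own time interaction so that it acts on the change in score. The cost is one degree of freedom: with 44 patients in two groups, 44 − 2 = 42 for error becomes 44 − 3 = 41. This change does not replace the first, because it cannot restore strata that were applied inconsistently at randomisation.
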